### Embedded qualitative work

A key aim of phase II of the MRC Complex Intervention Framework is to develop and test out interventions. We will conduct longitudinal qualitative work to help define the fundamental components of the intervention and to develop a step-by-step account of how the intervention evolves over time. The project researcher will attend monthly working meetings between the outreach workers and the management team to record discussions about activities undertaken, the response of the population to them, and changes made to work plans as they emerge. Furthermore, the outreach workers will be encouraged to keep detailed weekly records of what they do, which will form part of their regular progress reports to their supervisors at the stop smoking services. The project researcher will also shadow the outreach workers, making field notes while they engage in outreach activity on the streets and during promotional events and clinic sessions. Focus group discussions with the outreach workers will be carried out at quarterly intervals during data collection in order to:

◦ Define more clearly the role of the outreach worker in assisting Bangladeshi and Pakistani smokers to stop smoking

◦ Explore the approaches taken when recruiting service users and supporting smoking cessation and why they chose those particular approaches

◦ Understand how the service provided changes over time, as their role, and what does and does not work, becomes clearer.

One-to-one interviews with individual outreach workers will be carried out at the end of the study to capture any differences in ways of working.

We also aim to capture what happens in the pre-existing clinic based intervention (pharmacies), in order to be able to record how different the 'clinic + (outreach)' intervention is in terms of approaches to cessation support. Whilst it is often expected that there is a standard approach, in practice there is often surprisingly large variation. To this end we will carry out a small number of brief one-to-one interviews with a purposive sample of pharmacists in the study area to develop a clearer picture of any added value of the outreach worker intervention.

### Risks to the safety of service users in the trial

There are no anticipated risks to clients from participation in this study over and above those associated with using a smoking cessation service. Most participants will not even know that they are participating, as their routinely collected NHS data will be passed in anonymised form to the researchers. For patients participating in the Extended Dataset, there is the risk of inadvertent disclosure that they smoke to relatives that do not know this; however the study team are aware of this and will minimise this risk.

### Outcome measures and analysis

#### Proportion of people attending but not setting quit dates

Stop smoking services return only the number of people setting quit dates with the service, so these data are not routinely collected. To obtain these, we need to identify service providers in intervention and control areas that keep meticulous booking records. If we find such providers during the collection of the Extended Dataset, we will try to estimate the proportion of people who attend without setting a quit date. However, it is unlikely that booking records give the ethnic group of the person booking, so this may prove impossible. Should appropriate data be available, the number of quit days set in relation to the number of bookings will be examined using a Poisson multilevel model for intervention and control areas.

#### Denominator for the proportion of smokers setting quit dates

Our overall aim is to develop and refine the intervention, to pilot it, and have the data needed to inform sample size calculations for a definitive trial evaluating these interventions. In order to perform sample size calculations for a future trial, we aim to assess the reach of the interventions in attracting smokers wanting to quit. For the purposes of this study, reach has been defined as the proportion of each relevant ethnic group setting a quit date using the stop smoking service, with the denominator for this being all those of relevant ethnic group attempting to quit during the same period. We are estimating this latter number as it cannot be directly measured. We have searched a variety of sources to give information on the proportion of each ethnic group that attempted to quit in the past year and these data are not available. No local survey can truly randomly survey Pakistani and Bangladeshi populations because there is no publicly available local sampling frame that records ethnicity. Consequently, we will use the Smoking Toolkit Study to provide relevant data on the proportion of people that attempted to quit in the past year for the general population and assume that this figure is approximately the same in Pakistani or Bangladeshi men[34].

Stop smoking services routinely record information about each of their patients, including their age, gender, ethnic group, type of service used, medication used and outcome. This will be used to give both a before and after measure of the use of the service by the relevant groups (i.e. males of Pakistani and Bangladeshi ethnic group). Thus, we will have, for each area, the rate of use of the service for 12 months prior to the intervention that will serve as a baseline variable in the analysis (see Table 3). The after measure will be the same data collected for the 12 months during which the outreach workers are active. These data will be supplied anonymously from BEN and HoBt PCTs and this does not rely on data collection developed for the study. As noted above, the before-after design will allow control for intrinsic variability between areas. As such there will be no attempt to assess baseline balance between the intervention and control areas.

**Table 3 T3:** Use of LSSS by randomisation area residents for the baseline period (1st November 2006 – 31^st ^October 2007)

Area number	Number of Pharmacies	Numbers using any LSSS service 06/07	Number of smokers using LSSS within area they live	Number of smokers using LSSS in other areas of randomisation	Number of smokers* using LSSS users out of study zone	Number of smokers using unidentified LSSS
1	0	7	0	0	7	0

2	1	10	1	0	9	0

3	0	29	0	8	20	1

4	3	79	41	4	32	2

5	5	155	57	2	77	19

6	4	136	43	5	84	4

7	6	98	55	0	42	1

8	2	6	0	1	5	0

9	1	2	0	0	2	0

10	0	4	0	0	3	1

11	0	8	0	5	3	0

12	0	3	0	0	3	0

13	0	11	0	8	2	1

14	1	8	0	3	5	0

15	0	2	0	0	2	0

16	0	5	0	0	5	0

*Bangladeshi or Pakistani Males aged 18 years or over

Although we will estimate the proportion of people setting a quit date, we cannot truly know the denominator, as in many cases people set multiple quit dates, hence we will consider this a rate and the 'denominator' an offset in the analysis.

Quantitative analysis will use a multilevel approach. In this model the outcome variable will be the number of individuals setting a quit date in each of the 16 randomised areas. The quasi-denominator is the estimated number wishing to quit in each area, and the log of this number will be used as an offset in a Poisson regression model. Independent variables in the model will be the group (control or intervention) and the log of the numbers setting a quit date in the previous 12 months before the trial. The randomised areas will be included in the model as a random effect, thereby allowing for the clustering inherent in the design[35]. This will be used in estimating the intra-class correlation coefficient, which in turn will determine the design effect. This is the multiplier which has to be applied to standard sample size formulae to allow for the effect of randomising at the cluster level instead of the individual level[36]. The stratification used in producing the randomisation will not be utilised in the analysis.

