## Methods

### Study/design

This is a pilot cluster randomised controlled trial being undertaken in Birmingham East and North Primary Care Trust (BEN PCT) and the Heart of Birmingham Teaching Primary Care Trust (HoB tPCT). The trial compares the change in the key outcome variables between intervention and control areas. The change is the difference between the intervention period rates of activity in the intervention area and the same period one year prior to the intervention. An analogous figure is calculated for the control areas and the difference in these changes are then compared.

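### The uptake model adjusts a rate for the log of the baseline count instead of the baseline rate, so the before-after control the protocol relies on is largely not delivered

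*Protocol article*

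**What the plan says.** All of the following is in the Protocol article.

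- **Study/design** defines the comparison as a change in rates: "The change is the difference between the intervention period rates of activity in the intervention area and the same period one year prior". The same figure is formed for the control areas and the two changes are compared.
- **Denominator for the proportion of smokers setting quit dates** describes the baseline variable as "the rate of use of the service for 12 months prior to the intervention that will serve as a baseline variable in the analysis". It then states that "the before-after design will allow control for intrinsic variability between areas", and draws a consequence: "As such there will be no attempt to assess baseline balance between the intervention and control areas".
- The model specification in the same section reads differently. "In this model the outcome variable will be the number of individuals setting a quit date in each of the 16 randomised areas"; the estimated number wishing to quit is the quasi-denominator, and "the log of this number will be used as an offset in a Poisson regression model". The covariates are trial arm and "the log of the numbers setting a quit date in the previous 12 months before the trial". Area is a random effect, its variance feeds the intra-class correlation and design effect, and the randomisation strata are left out of the model.
- **Definition and modelling of abstinence rates** says that the abstinence models follow the same approach, with logistic in place of Poisson regression.

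**The concern.** An offset has its coefficient fixed at 1, so the model describes each area's rate. The baseline covariate has no denominator. A large area with a low rate and a small area with a high rate can therefore have the same baseline count, although their expected rates differ. No other term in the model separates size from rate.

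If the covariate carries mainly size, it cannot absorb lasting differences in uptake between areas. Those differences stay in the residual, the arm comparison is less precise than the design allows, and a chance difference in baseline rates between eight and eight areas is left largely uncorrected. That is the very protection the protocol cites when it declines to examine baseline balance.

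**Working it through.** **Inputs from the protocol.** The outcome, offset and covariate are as set out above. Baseline counts are from Table 3, taken as the baseline quit-date counts. The population cuts of 300 and 10,000 are from Randomisation. The protocol gives no power, precision or effect size for this model, so there is no figure of its own to reproduce. The 16 Table 3 counts sum to 563.

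**Inputs not in the protocol (assumed).** These are the area denominators N, the between-area SD of the log rate s_r, and the year-to-year correlation of area rates ρ.

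**Step 1: what the coefficient can do.** Write Y0 and Y1 for the baseline and trial-year counts, and r0 for the baseline rate.

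- The model is log E[Y1] = log N + a + b·arm + c·log Y0.
- Since log Y0 = log N + log r0, the modelled log rate is a + b·arm + c·(log N + log r0).
- Size is already in the offset, so log N needs a coefficient near 0. Where rates persist, log r0 needs one near 1. A single c must serve both.
- If log N and log r0 are independent, c tends to ρ·s_r² / (s_N² + s_r²), where s_N is the SD of log N.

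**Step 2: how much of the log count is rate.** In Table 3 the counts run from 2 to 155 (155/2 = 77.5-fold). Four areas hold 79 + 155 + 136 + 98 = 468 of 563 users (83%). The variance of the log counts is 2.17 (SD 1.47). The share that rate variation could explain is s_r²/2.17:

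| s_r | Share of variance of log count |
|---|---|
| 0.3 | 0.09/2.17 = 4% |
| 0.5 | 0.25/2.17 = 12% |
| 0.8 | 0.64/2.17 = 29% |
| 1.0 | 1.00/2.17 = 46% |

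The rest is size and Poisson noise. At s_r = 0.5 and ρ = 0.95, c is about 0.95 × 0.115 = 0.11 on the Table 3 variance. With an assumed SD of log N of 1.8 it is 0.95 × 0.25/(3.24 + 0.25) = 0.07.

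**Step 3: effect on precision.** The stated model was simulated with assumed populations and the baseline total set to 563. The fitted slope was 0.02 to 0.18 with the log count and 0.43 to 0.92 with the log rate. The variance of the log rate ratio with the count, relative to the rate, was about 1.1 at a log-rate SD of 0.2, about 2.4 at 0.4, and 3.6 or more at 0.6 and above. A second set of runs with the same total (60 per scenario) gave 1.1–1.2 at 0.2, 1.4–1.6 at 0.3, 2.0–2.5 at 0.5 and 2.6–5.4 at 0.8. The direction and the rise with rate variation agree; the exact ratios move with the assumptions.

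**Step 4: effect on the between-area variance.** Further runs (150 per scenario) assumed populations of 3,000–10,000, 10,000–15,000, 100–300 and 300–1,000 in the four strata, and 2% uptake. At s_r = 0.5 and ρ = 0.95:

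| Baseline term | Between-area variance | SD of log rate ratio |
|---|---|---|
| None | 0.200 | 0.290 |
| Log count (as written) | 0.181 | 0.284 |
| Log rate | 0.029 | 0.141 |

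The count removes (0.200 − 0.181)/0.200 = 10% of the variance and the rate 86%. Across the scenarios run, the ranges were about 8–19% and 58–89%. These runs imply more users than Table 3: the stratum midpoints 6,500 + 12,500 + 200 + 650 = 19,850, times 4 areas, times 0.02, give 1,588 against 563. They therefore flatter the rate version. They are used here only to show that the count version lies close to no adjustment.

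**The case against.** **The wording is loose.** The sentence that promises a baseline rate points to Table 3, which holds counts only, so rate may be meant informally there. That softens the textual conflict. It does not change the model, in which a count is paired with an offset, or the definition of change in Study/design.

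**The count is not only size.** This is correct: it contains the baseline rate, so some adjustment remains, and more if rates vary widely relative to populations.

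**Bias.** A reader might infer that the arm comparison is biased or that area differences go uncontrolled. The protocol does not support that. Randomisation is stratified by density and population size, community-level data such as socio-economic position are collected, and randomisation protects against bias on average. Leaving the strata out of the model does not undo the balance they give to the allocation.

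**The design effect.** A reader might also infer that the variance passed to the definitive trial is inflated. The protocol says the design effect multiplies standard sample size formulae, and without covariates those need the unadjusted variance. The model as written gives something close to that (0.181 against 0.200 in Step 4). It is too large only if the definitive trial will also adjust for baseline rate, which the protocol does not say.

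**It is a pilot.** No decision threshold or power rests on this model, and the arm effect can still be estimated. This limits the severity and stands.

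**Conclusion.** The point holds as a mis-specified covariate and an inconsistency within the protocol. With the offset in place, the log baseline count does little more than no baseline term, so the before-after control claimed for the analysis is largely absent, and the decision not to assess baseline balance loses its stated ground.

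The cost is in precision and control of chance imbalance. It ranges from negligible, if area rates hardly differ (log-rate SD near 0.2), to a several-fold variance if they differ substantially (0.6 and above). This rests on assumed area populations, on uptake scaled to 563 baseline users, and on area rates that persist from year to year. It should be fixed, but it does not invalidate the trial.

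**What to change.** 1. In the model specification, replace the covariate with log(baseline quit dates / baseline denominator), keeping the offset. No Table 3 count is zero, so the log is defined for every area.
2. Make Study/design, the description of the baseline variable and the model specification say the same thing.
3. Report the between-area variance both unadjusted and adjusted for baseline rate, so that the definitive trial can use the one that matches its own analysis.
4. In the abstinence model, state that the baseline term is a baseline proportion or logit.

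An alternative to item 1 is to keep the log count and add the log denominator with a free coefficient. This nests the rate model rather than equalling it, and costs one more parameter with 16 areas. As a sensitivity analysis, fit both periods together with a group-by-period term and random effects for area and for area-by-period; the group-by-period term is then the ratio of changes, the log-scale counterpart of the comparison in Study/design.

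The cost is a line or two of specification and no new data. Because Current study status says that analysis is under way, the change should be recorded as an amendment before results are final.

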### Randomisation

We will use census super output areas (SOAs) as the unit of allocation[30]. In order to define these communities, initially all those SOAs within the study area with a combined Bangladeshi and Pakistani population of more than 10% will be identified and then mapped at ward level, enabling the street boundaries of each SOA to be seen. Contiguous SOAs will then be aggregated into natural communities (i.e. areas where people live, work, shop etc) using the local knowledge of the LSSS managers and advisors. SOAs in which more than 30% of the population are Pakistani and Bangladeshi will be considered to be high-density areas, while SOAs with 10–29% of the population being from these groups will be defined as low-density areas.

A total of 16 aggregated areas, sufficiently geographically dispersed, will be created to be randomised; there will thus be eight SOAs in each arm. For the randomisation, we will stratify, firstly by the proportion of Pakistani and Bangladeshi residents and secondly by absolute population size, to create eight areas that include high target population density and eight that are low-density areas. The high density areas will be further subdivided into those areas with target populations of Bangladeshi and Pakistani men above and below 10,000. The low density areas will be further subdivided into those areas with target populations above and below 300. Table 1 shows how the areas will be allocated. Randomisation will be undertaken by the study statistician who has no knowledge of the geographical areas using permuted blocks. Within each of the four strata, two areas will be randomly allocated to 'control' and two to 'intervention' arms. Maps of the final areas and their allocation to the two study arms are shown in Figures 1 and 2.

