#### Definition and modelling of abstinence rates

The quit rate is defined as the proportion of people achieving abstinence, with a denominator of all those who attended the service and set a quit date. Quitting is defined as prolonged abstinence, which is defined as allowing lapses during the first two weeks of the quit process measured according to the Russell standard[37]. Self-reporting is substantiated by biochemical validation using expired carbon monoxide (less than 10 parts per million)[38].

The modelling will follow the same approach as described above for calculation of usage rates, except that we will have a true denominator. We will therefore use multilevel logistic regression models rather than Poisson models.

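### With 16 very unequal areas, an area random effect does not by itself allow adequately for clustering: standard large-sample inference for the arm effect is too narrow

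*Protocol article*

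**What the plan says.** Under Randomisation, the protocol article states: "A total of 16 aggregated areas, sufficiently geographically dispersed, will be created to be randomised". It adds: "Within each of the four strata, two areas will be randomly allocated to 'control' and two to 'intervention' arms".

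The analysis is set out under Outcome measures and analysis, in the section on the denominator for the proportion setting quit dates. There "the outcome variable will be the number of individuals setting a quit date in each of the 16 randomised areas". A log offset carries an estimate, area by area, of how many smokers want to stop. Study arm and the logged count from the baseline year are the only covariates. On clustering, the section says: "The randomised areas will be included in the model as a random effect, thereby allowing for the clustering inherent in the design". The same random effect is to supply the intra-class correlation and the design effect, and the section ends by leaving the randomisation strata out of the analysis.

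For abstinence, under Definition and modelling of abstinence rates: "The modelling will follow the same approach as described above for calculation of usage rates, except that we will have a true denominator". The Poisson model becomes a multilevel logistic one.

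No estimator, test, significance level or interval method is named for any of these models.

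**The concern.** The Study/design section says that the arms are compared on change in the key outcomes, and group is a term in the model. The arm effect has to be judged against variation between areas, and the random effect is the only device offered for that.

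Standard likelihood inference from such a model treats the between-area variance as if it were well estimated from many areas. Here it comes from 16 single counts after three parameters have been fitted, and most of the information sits in four or five areas. Maximum likelihood then tends to put the variance too low, and a normal reference ignores the uncertainty in it.

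Two things are at stake. The interval for the outreach effect would look more certain than the data allow. The design effect, which primary study question 3 asks for, would rest on a poorly determined variance quoted without its uncertainty.

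**Working it through.** The article gives no power, error rate or variance figure on this point, so there is nothing of its own to reproduce.

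**Inputs from the article**
- 16 areas, allocated 2:2 in each of four strata.
- Table 3, column headed "Numbers using any LSSS service 06/07": 7, 10, 29, 79, 155, 136, 98, 6, 2, 4, 8, 3, 11, 8, 2, 5. The total is 563. Areas 4 to 7 hold 79 + 155 + 136 + 98 = 468, and 468/563 = 83%. Eleven areas have 11 or fewer.
- Fixed effects: intercept, group and log baseline count, leaving 16 − 3 = 13 residual degrees of freedom.

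**Assumptions, because the article gives no value**
- Between-area SD of log rates from 0 to 0.8.
- Area offsets either exactly proportional to the baseline count or with added log-scale error of SD 0.5.
- Strata formed by ranking the baseline counts.
- A two-sided nominal 5% test.

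**Benchmark without simulation.** Suppose all areas were equally informative. Maximum likelihood divides the residual variance by 16 where 13 is unbiased. A z test at 1.96 is then a t test on 13 df at 1.96 × √(13/16) = 1.767, and P(|t₁₃| > 1.767) = 10.1%. The direction therefore does not depend on the unequal counts.

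**Simulation under no outreach effect.** Counts were drawn as Poisson with mean equal to the Table 3 count times exp(u), with u normal with mean 0 and the stated SD. The planned model was fitted by maximum likelihood (adaptive quadrature) in 2,000 trials per setting; the Monte Carlo standard error is about 0.5 to 0.9 points. Each cell gives rejection (%) with the exact offset, then with the noisy offset. The randomisation test uses observed minus expected counts within strata.

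| SD | Wald z | Likelihood ratio | Randomisation test |
|---|---|---|---|
| 0 | 4.5 / 12.0 | 3.7 / 8.8 | not run |
| 0.1 | 13.2 / 14.3 | 10.0 / 11.1 | 5.25 / 4.85 |
| 0.2 | 19.2 / 12.9 | 13.1 / 9.9 | 5.35 / 5.35 |
| 0.3 | 18.8 / 13.4 | 12.4 / 10.2 | 4.95 / 5.4 |
| 0.5 | 14.1 / 11.8 | 10.9 / 8.9 | 5.65 / 5.1 |
| 0.8 | 9.3 / 10.3 | 7.9 / 8.4 | 5.2 / 5.7 |

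**Variations**
- Separate code with 1,000 trials per setting and an exact offset gave Wald rejection of 10.8%, 18.7%, 16.6% and 14.4% at SD 0.1, 0.2, 0.3 and 0.5. It gave 14.9% at SD 0.2 with offset error of SD 0.4. At SD 0.2 with the exact offset the mean standard error was 0.133 against a true SD of 0.177, a ratio of 0.75.
- With half of the area variance placed between strata (800 trials), Wald rejection was 19.6%, 17.3% and 12.5% at SD 0.2, 0.3 and 0.5.
- Replacing z by t on 13 df in the maximum-likelihood fit still gave 7–16% over SD 0.1 to 0.8.
- REML-type estimation (penalised quasi-likelihood, 600 trials) with a z test gave 9.2%, 11.0%, 11.5% and 11.0% at SD 0.1, 0.2, 0.3 and 0.5 with the exact offset, and 6–9% with the noisy offset. Adding a t₁₃ reference gave 7–10.5% and 4–7% respectively.

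**Variance component.** With the exact offset it was estimated as essentially zero in 61%, 28% and 12% of trials at true SD 0.1, 0.2 and 0.3. With the noisy offset this happened in about 2% or fewer, because offset error adds to the apparent area variance.

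**Zero counts.** With Table 3 counts as Poisson means, the chance that at least one area has a zero count is 1 − ∏(1 − e^−m) = 31%, before any extra variation.

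**The case against.** The strongest objection is that the criticised inference is not in the article. It names a model, offset, covariates and random effect, and nothing on estimator or test. Those details commonly sit in a statistical analysis plan, and their absence is no fault here. The sentence about clustering can be read simply as a description of model structure, and as such it is right. What remains is that the article presents the random effect as sufficient and also rules out the strata, which are the natural basis for a small-sample test.

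A reader might infer that this trial's test has an error rate of 11–19%. The documents do not support that. Figures near 19% need maximum likelihood, a Wald test, an SD of about 0.2 to 0.3 and an offset exactly proportional to past service use, whereas the article defines the offset as the number wishing to quit. With REML-type estimation the inflation is smaller, and with a t reference and a noisy offset it nearly disappears.

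A reader might also infer that a false-positive outreach decision is the main risk. This is a pilot with no stated significance level or decision rule, and its aims are refinement and sample-size inputs. Over-narrow intervals and an uncertain design effect matter more.

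Finally, the abstinence models were not simulated, so no figure can be attached to them. Nor do the results justify discarding model-based intervals altogether.

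**Conclusion.** The concern holds in conditional form. With 16 single counts this unequal and three fixed effects, an area random effect combined with standard large-sample inference gives intervals for the uptake comparison that are too narrow.

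For SD 0.1 to 0.5, the nominal 5% test rejects roughly 10–19% with maximum likelihood and Wald z (10.8% to 19.2% observed), 8–13% with a likelihood-ratio test, and 6–12% with REML-type estimation and a z test. Under maximum likelihood it is near 5% only if there is no extra-Poisson variation and the offset is exact. These sizes rest on the assumed SDs, offsets and strata; the direction does not. The concern carries over to abstinence in direction only. It is a cheap improvement to the analysis, not a flaw that invalidates the design.

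**What to change.** Keep the multilevel Poisson and logistic models for point estimates and variance components. Change the inference for the arm effect as follows.

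- Fit the model without the arm term (offset and log baseline count), and take observed minus expected counts per area. This is defined when a count is zero, which a log-rate statistic is not.
- Take the absolute arm difference in these residuals, and re-allocate areas 2:2 within the four strata: 6⁴ = 1,296 allocations. Because the statistic is unchanged when all arm labels are exchanged, the switch of arms reported under Protocol amendments does not disturb it.
- Obtain the interval by inverting the test over candidate rate ratios.
- Show model-based intervals, if wanted, as secondary with a small-sample caveat.
- Report the between-area variance, intra-class correlation and design effect with intervals, since the variance may well be estimated as zero.

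Reword the clustering sentence so that it describes the model only, and amend the statement that the strata are not used. No new data are needed. The cost is wider intervals and a short program.
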